## STATISTICAL ANALYSIS PLAN – CURRENT STUDY

### Power calculation

Power analyses: The trial was powered according to the primary outcome of persistent wheeze/asthma. The statistical power of the nested RCT on neurodevelopment was calculated *post-hoc* based on the eligible children for such sub-analysis. A total of 551 children were included in the neurodevelopmental outcome assessment and 503 of these completed the BSID-III. The power calculation based on 503 children demonstrated over 80% power ( $\alpha=0.05$ , two-tailed) to detect a 5 points difference in the mean Cognitive Composite score (equivalent to 0.33 SD) between the two intervention groups.

### Statistics

Probabilistic principal component analysis (pPCA) was used to generate principal *components* (PCs) for the milestone data assuming that missing values were missing at random. The PCs were used to assess if there was an overall effect on milestone development with subsequent analyses by linear regression analysis of individual milestones.

The effect of the high-dose vitamin D3 intervention on language development were assessed using Quasi Poisson regression models. The intervention's effect on Bayley-III cognitive composite score was assessed using linear regression models, while the effect on ASQ-3 general neurodevelopment was analyzed using Wilcoxon rank sum test.

The SDQ scores for total difficulties were divided into two groups: children with fewer and/or milder problems (values  $\leq$  median) and children with increased and more severe problems (values  $>$  median). The scores rating the functional impact of existing emotional and behavioral problems were grouped according to no or any impact. The effect of the high-dose vitamin D3 intervention on the SDQ scores was determined using logistic regression models.

All analyses were adjusted for maternal pre-intervention serum vitamin D3 levels, season of birth, sex, and n-3 LCPUFA RCT allocation.

Results are reported with 95% confidence intervals (CI), and 2-sided p-values. Missing data was treated as missing observations, except in the milestone pPCA.

The data processing was conducted using R version 3.5.2 (R core team 2018).

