## **Method and trial procedure**

The women are recruited from the COPSAC2010 cohort; Local Ethics Committee (H-B-2008-093), Danish Data Protection Agency (2015-41-3696).

The study is a double-blinded, placebo-controlled, randomized parallel group design. 800 pregnant women will be randomized in a 1:1 ratio to intake of either high dose vitamin D supplementation or placebo according to one of the following regimes:

- 1) Placebo (+ guidance in recommended supplement of vitamin D (400 units daily)) or
- 2) High dose vitamin D supplement (2400units daily) (+ guidance in recommended supplement of vitamin D (400units daily))

The regimes are administered orally as 2 tablets daily.

Blinding and randomization are carried out by the Capital Region Pharmacy and stratified according to treatment group in the fish oil intervention study (ClinicalTrials.gov: NCT00798226). This allows for equal numbers receiving high dose vitamin D supplementation in both the fish oil active group and the fish oil placebo group.

The intervention is initiated at the beginning of the third trimester (pregnancy week 24) and continued until 1st visit to the COPSAC clinic after birth at week 1-2 postpartum. At the clinical visit in pregnancy week 24, the women will be provided with the intervention treatment and interviewed about current daily vitamin D intake and history of diseases likely to influence vitamin D levels. At pregnancy week 36 adherence to the regime will be assessed by interview at the COPSAC clinic. Furthermore, the women will be instructed to return the remaining tablets at the end of the intervention for evaluation of their compliance.

At pregnancy week 24 and 1st visit after birth a blood sample will be drawn from the mother in order to measure 25-OH-vitamin D, total calcium, parathyroid-hormone (PTH) and alkaline phosphatase.

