Secondary analyses: 1) Milestone development monitored prospectively by the parents using a registration form based on The Denver Development Index and WHO milestones registration (combined assessment by principal component analysis); 2) Language development assessed at 1 and 2 years of age with the Danish version of The MacArthur Bates Communicative Developmental Inventory (CDI); 3) The child's general development (language, fine and gross motor, social and problem solving) at 3 years of age assessed with Ages and stages Questioner, third edition (ASQ-3)

Growth:

Body composition: Body composition measured as fat mass, lean mass, bone mineral content (BMC) and bone mineral density assessed (BMD) through DXA scans at 6 years of age.

Anthropometrics: Clinical follow up on the development of weight in kg (calibrated digital weight scales), height in cm (Harpender stadiometer), waist-, thorax- and head circumference in cm (using tape; 3 times each) at every visit till age 10 years assessed longitudinally in the research clinic.

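### ASQ-3 is assigned a plain Wilcoxon rank sum test, which cannot carry the covariate adjustment the SAP claims for all analyses, and no ASQ-3 effect measure is named for the promised 95% CI

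*Supplement*

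**What the plan says.** Three sentences in the Statistics section of the current SAP bear on this point.

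- Method: "the effect on ASQ-3 general neurodevelopment was analyzed using Wilcoxon rank sum test".
- Adjustment: "All analyses were adjusted for maternal pre-intervention serum vitamin D 3 levels, season of birth, sex, and n-3 LCPUFA RCT allocation".
- Reporting: "Results are reported with 95% confidence intervals (CI), and 2-sided p-values".

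The last adjustment factor is also the randomization stratum. Under Method and trial procedure, the protocol says that allocation is "stratified according to treatment group in the fish oil intervention study".

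ASQ-3 is listed among the secondary analyses of neurological development, as the child's general development "at 3 years of age assessed with Ages and stages Questioner, third edition (ASQ-3"). The protocol's outcome 8 gives it the same place. The main neurodevelopment analysis is the Bayley-III cognitive score.

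**The concern.** The adjustment sentence covers every analysis, and the method named for ASQ-3 cannot comply with it. An analyst must break one of the two sentences, and the SAP does not say which. The ASQ-3 result could therefore be unadjusted, stratified by fish-oil group only, or adjusted by a method the plan does not name.

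The reporting sentence leaves a second gap. An interval needs an estimate, and none is named for ASQ-3. If the result is null, readers need that interval to judge how much benefit or harm has been excluded. They also need to know whether it is adjusted.

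**Working it through.** **Step 1. Can each named method carry the covariates?** All methods are from the Statistics section of the current SAP.

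| Outcome | Named method | Takes the four covariates? |
|---|---|---|
| Bayley-III cognitive score | linear regression | yes |
| Language | quasi-Poisson regression | yes |
| Individual milestones | linear regression | yes |
| SDQ | logistic regression | yes |
| ASQ-3 | Wilcoxon rank sum test | no |

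ASQ-3 is the only one of these whose method has no place for covariates. A stratified rank test (van Elteren) could take the fish-oil stratum, but it could not take vitamin D as a continuous level, and the SAP does not name it. The section does write an exception where it wants one: the milestone pPCA is exempted from the missing-data rule. It writes none for ASQ-3.

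**Step 2. The plan's own figure.** The only power statement is for Bayley-III: over 80% for 5 points (0.33 SD), two-sided alpha 0.05. The Power calculation section gives the counts: "A total of 551 children were included in the neurodevelopmental outcome assessment and 503 of these completed the BSID-III". Assume 503/2 = 251.5 per group, since the protocol plans that "800 pregnant women will be randomized in a 1:1 ratio", and SD = 5/0.33, about 15.

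- Standardized SE = sqrt(2/251.5) = 0.0892
- Noncentrality = (5/15)/0.0892 = 3.74
- Power = Phi(3.74 - 1.96) = Phi(1.78) = 0.96

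The statement is correct, but it does not bear on ASQ-3, for which no sample size or power is given.

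**Step 3. Size of the effect on ASQ-3, by simulation.** All inputs are assumptions: n = 503 (251 and 252), a normal outcome with unit variance, a shift of 0 or 0.25 SD, and covariates explaining 0 to 20% of the variance; 2,000 runs per setting. The plain rank sum test is compared with linear regression of the ranks on treatment and four covariates.

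| Variance explained | Type I error, plain | Type I error, adjusted | Power, plain | Power, adjusted | Difference (points) |
|---|---|---|---|---|---|
| 0% | 5.2% | 5.3% | 79.2% | 78.7% | -0.5 |
| 5% | 5.7% | 6.0% | 76.8% | 79.1% | 2.3 |
| 10% | 4.4% | 4.8% | 78.1% | 81.9% | 3.8 |
| 20% | 5.3% | 4.9% | 76.6% | 85.5% | 8.9 |

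The Monte Carlo standard error is about sqrt(0.05 x 0.95/2000) = 0.5 points for type I error and sqrt(0.78 x 0.22/2000) = 0.9 points for power. Type I error is near 5% throughout. The power cost of not adjusting is about 0 to 9 points. The simulation used simple rather than stratified allocation and gave the fish-oil indicator no effect of its own, so it shows the cost of omitting prognostic covariates in general, not of that stratum in particular.

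**Step 4. Can the named test supply an interval?** Yes. The Hodges-Lehmann shift is the median of all between-group differences. Its 95% limits are the k-th smallest and k-th largest differences, with k = n1 x n0/2 - 1.96 x sqrt(n1 x n0 x (n1 + n0 + 1)/12). With 252 and 251 children, k = 31,626 - 1.96 x 1,629.9, which truncates to 28,431 of 63,252 differences. One simulated data set with a true shift of 0.25 SD gave 0.29 SD (95% CI 0.10 to 0.46). The CI promise can therefore be kept with this test, but the estimate is unadjusted and the SAP does not name it.

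**The case against.** The strongest reply is that little depends on this. ASQ-3 is one secondary analysis within a secondary outcome domain, the trial's primary outcome is persistent wheeze, and the main neurodevelopment analysis uses a regression that carries all four covariates. Randomization protects the unadjusted test. The counts in the SAP are already known, so a new model for ASQ-3 would be a post-hoc choice. These points stand. They lower the severity and argue for keeping the named test in the report, but they do not reconcile the two sentences.

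A reader might infer more than the documents support:

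- **That ASQ-3 was left unadjusted.** This follows only if the test was run exactly as named. The SAP contradicts itself and does not settle the matter.
- **That a Wilcoxon analysis yields only a p-value.** Step 4 shows otherwise. The gap is that no effect measure is specified.
- **That adjustment would shrink the standard error by sqrt(1 - R2).** That is a linear-model result. In a proportional-odds model, adjustment does not shrink the standard error of the log odds ratio in this way; the gain in power comes from the conditional log odds ratio lying further from zero.
- **That five separate domain tests are affected.** The outcome lists name five areas in parentheses, but the Statistics section refers to ASQ-3 general neurodevelopment and does not say whether areas are tested singly or as a total.

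**Conclusion.** The inconsistency is real, lies within one section, and is not resolved elsewhere in the supplement. As written, ASQ-3 cannot be both analyzed by a plain rank sum test and adjusted for four covariates, and the promised interval has no named estimate. No bias or inflated type I error is shown.

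The practical costs are a misleading description of the result and a power loss of about 0 to 9 points. That range rests on the assumptions in Step 3, none of which the documents give for ASQ-3. Severity is moderate: the text should be corrected, but no primary or main neurodevelopment conclusion depends on it.

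**What to change.** **Preferred.** Make the ASQ-3 analysis a proportional-odds or rank-based regression with treatment and the four stated covariates. Name its effect estimate (for proportional odds, a conditional odds ratio) and report it with a 95% CI. Keep the Wilcoxon test, with a Hodges-Lehmann shift and 95% CI, as a labelled unadjusted analysis, so that the originally named test is still shown. State whether the developmental areas are analyzed singly or as a total, and record the date and reason for the change.

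**Minimum.** Exempt ASQ-3 explicitly from the adjustment sentence, and name the Hodges-Lehmann shift with 95% CI as its estimate.

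**Cost.** Either repair takes a sentence or two in the SAP and a few lines of R, and needs no covariates beyond those the other models already use. The preferred version adds a proportional-odds assumption to check (if that model is chosen) and targets a conditional rather than a marginal effect, which the report should say.

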### Summary of changes

Addition of milestone-, language-, cognitive development and general neurodevelopment data to the original statistical plan. Power calculation was performed based upon the available number of children available for the current study.
